### Procedures

#### Data collection

Genetic counseling providers who meet the eligibility criteria and provide written consent will complete a 15-min baseline survey online before their first recorded appointment with a participating patient. The provider baseline survey is designed to assess all four types of bias as well as covariates that are likely to be associated with patient-provider communication, clinical discussion, and/or patient-centered outcomes, including demographic information, professional information, and prior training experiences. Genetic counseling providers will also complete a 1-min post-encounter survey after each genetic counseling encounter with a participating patient. Patients who meet the eligibility criteria will complete a 45-min baseline survey over the phone following the consent and HIPAA authorization and before the scheduled appointment with their participating genetic counseling provider. The patient baseline survey is designed to assess covariates that are likely to predict patient-provider communication, clinical discussion, and/or patient-centered outcomes. After their appointment, patients will complete a 5-min post-encounter survey. Table 2 provides an overview of the variables assessed in the surveys.

**Table 2 Tab2:** An overview of the variables assessed in the surveys

	Genetic counseling providers	Patients
**Baseline**	• Demographic information • Professional information • Implicit racial prejudice • Explicit racial prejudice • Implicit racial stereotyping • Explicit racial stereotyping	• Demographic information • Socioeconomic information • Perceived racial discrimination • General trust in genetic providers • General satisfaction with healthcare
**Post-encounter**	• Therapeutic alliance	• Therapeutic alliance • Provider-specific trust • Provider-specific satisfaction • Perceived empowerment
**Medical chart**		• Genetic test uptake

On the day of the appointment, the patient-genetic counseling provider clinical encounter will be video- and audio-recorded. *For patients who have appointments in-person*, we will use two GoPro10 cameras (one focusing on the patient, another focusing on the provider) mounted on the wall with Velcro. These portable devices are designed to minimize intrusiveness while capturing patient-provider communication. We will attach the two cameras to the walls of the consultation room prior to the patient entering. The genetic counseling provider and patient will meet as scheduled while we control the recording from outside of the room using a GoPro device called The Remote [45]. Additionally, a digital voice recorder will capture audio of the interaction to be used in the unlikely event that the video fails. After each encounter, the genetic counseling provider will complete a 1-minute post-encounter survey, and the patient will be escorted to another room to complete a 5-minute post-encounter survey. Both the provider and the patient will be given three options to complete the survey: [1] paper and pencil, [2] a tablet with optional stylus, and [3] a QR code to scan and complete the survey on a personal device.

*For patients who have appointments via telehealth*, we will record the encounters locally on a laptop using Camtasia® screen capture software [46]. We will join the virtual appointment with both camera and microphone turned off. The patient and provider will meet as they typically would, and we will capture a screen recording of the appointment using Camtasia. Immediately after the telehealth encounter, the provider will receive a link to the provider post-encounter survey, and the patient will receive a phone call to complete the patient post-encounter survey over the phone. Providers will receive $30 after completing the provider baseline survey, and patients will receive $30 after completing the post-encounter survey.

Finally, we will review electronic medical records to assess whether patients agreed to take a genetic test after the recorded pre-test genetic counseling session. We will also assess genetic testing completion up to 6 months after the recorded genetic counseling session by reviewing patient electronic medical records (0 = test not completed, 1 = test completed).

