Continuous: Likert scale	*Patient-provider communication* (Provider communication style; The overall quality of patient-provider communication)	Linear regression with GEE
Continuous: Frequency	*Patient-provider communication* (Each type of silence; Each type of adjacency pairs; Each type of problems)	Poisson regression with GEE
Continuous: Proportion	*Patient-provider communication* (Topics initiated by providers; Primary units allocated to providers; Silence followed by provider talks; Repairs initiated by providers; Problems repaired by providers)	Linear regression with GEE
Continuous: Duration	*Patient-provider commu*nication (Each type of silence) *Clinical discussion con*tent (The amount of time spent on discussing a given topic)	Linear regression with GEE
Dichotomy	*Clinical discussion content* (The presence/absence of a given discussion topic)	Logistic regression with GEE
Multiple categories	*Patient-provider communication* (The primary units of turns)	Multinomial logistic regression with GEE

Finally, Aim 4 (to quantify the impact of patient-provider communication/clinical discussion content with patient-centered outcomes) examines Paths E and F in our conceptual model. The analyses will be carried out in steps similar to those in Aim 3. In Step 1, we will identify covariates associated with patient-centered outcomes by computing correlations among all aspects of patient-provider communication/clinical discussion topics and factors assessed in the patient baseline survey, the provider baseline survey, and the provider post-encounter survey. In Step 2, we will compute partial correlations between all aspects of patient-provider communication/clinical discussion topics identified in Aims 1 and 2 and patient-centered outcomes while controlling for covariates identified in Step 1. In Step 3, we will conduct a linear regression with GEE and Bonferroni correction for each self-reported outcome (e.g., trust, satisfaction, therapeutic alliance) and a logistic regression with GEE for behavioral outcome (genetic testing completion). All regressions will include the same set of predictors (aspects of patient-provider communication/clinical discussion topics that remain significant in Step 2, and care modality) and covariates. Aspects of patient-provider communication/clinical discussion topics that remain significant in Step 3 are considered as potentially important intervention points for reducing racial disparities in patient-centered outcomes.

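### Patient post-encounter survey mode is fully determined by care modality, so Aim 4 modality differences in patient-reported outcomes cannot be attributed to telehealth

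*Protocol article*

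**What the plan says.** The Protocol article, under Data collection, sets the survey mode by type of visit. For in-person appointments the patient is taken to another room, and "Both the provider and the patient will be given three options to complete the survey": paper, a tablet, or a QR code opened on a personal device. For telehealth appointments, "the patient will receive a phone call to complete the patient post-encounter survey over the phone", and no self-completed route is described for that patient. In the same sentence "the provider will receive a link to the provider post-encounter survey", so the provider version is self-completed in both settings.

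The patient post-encounter survey carries therapeutic alliance, provider-specific trust, satisfaction, perceived empowerment, perceptions of genetic testing, decisional conflict and the stated testing decision (Measures, Patient post-encounter survey). Testing completion has another source: "We will also assess genetic testing completion up to 6 months after the recorded genetic counseling session by reviewing patient electronic medical records".

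For Aim 4, the Statistical analysis section says that "we will conduct a linear regression with GEE and Bonferroni correction for each self-reported outcome", and then: "All regressions will include the same set of predictors (aspects of patient-provider communication/clinical discussion topics that remain significant in Step 2, and care modality". Step 1 looks for covariates among factors from the two baseline surveys and the provider post-encounter survey. Step 2 computes partial correlations controlling for the covariates found in Step 1. Care modality is first named in Step 3. No survey-mode variable and no modality interaction is stated for Aim 4.

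**The concern.** Patients may answer questions about trust in, or satisfaction with, a provider differently over the phone than alone on a form. Here the two modes never overlap: all telehealth patients are phoned and no in-person patient is. Any difference between the groups on these scales is then some mixture of visit type and way of asking, and no later analysis of the data can split it.

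Three things could be affected. The first is the reading of the modality coefficient, which is estimated in every Aim 4 regression. The second is the Step 2 filter, which decides which communication aspects and topics go forward to Step 3 and does not list modality among its controls. The third is the communication-outcome slopes in Step 3, if phone answers bunch at one end of the 1 to 5 scales, because the Aim 4 model assumes one slope for both modalities.

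**Working it through.** The plan states no figure on this point, so there is nothing to reproduce. The questions are whether the two effects can be separated, and where a mode effect would go.

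**Inputs from the documents:** 220 patients; survey mode by visit type as above; modality as a main effect in Aim 4 Step 3; modality not named in Steps 1 and 2.

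**Assumptions, not in the documents:** half the patients by telehealth (p = 0.5); true communication slope b = 0.30; true modality effect 0; communication score 0.5 SD lower in telehealth (δ = −0.5); within-modality SD of the communication score 1; mode shift m of 0.2, 0.3 or 0.5 residual SD; no clustering within provider.

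**1. Separability.** With columns for intercept, telehealth and phone survey, the last two are identical. The design matrix has rank 2 of 3, so only the sum of the two effects can be estimated.

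**2. Step 3, constant shift.** With modality in the model, its coefficient estimates 0 + m, that is 0.20, 0.30 or 0.50, although the true modality effect is 0. The communication slope stays at 0.30. Simulation (4,000 data sets of 220 per scenario) gave modality coefficients of 0.199, 0.299 and 0.501, and slopes of 0.299 to 0.301.

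**3. Step 2, constant shift, modality left out.** The slope becomes b + m × Cov(c, t) / Var(c), where c is the communication score and t the telehealth indicator.
- Cov(c, t) = δ p(1 − p) = −0.5 × 0.25 = −0.125
- Var(c) = 1 + δ² p(1 − p) = 1 + 0.25 × 0.25 = 1.0625
- Ratio = −0.125 / 1.0625 = −0.118

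| Mode shift m | Slope by formula | Simulated |
|---|---|---|
| 0.2 | 0.30 − 0.024 = 0.276 | 0.276 |
| 0.3 | 0.30 − 0.035 = 0.265 | 0.263 |
| 0.5 | 0.30 − 0.059 = 0.241 | 0.241 |

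The sign depends on the assumption. If communication scores were 0.5 SD higher in telehealth, m = 0.3 would give 0.30 + 0.035 = 0.335. If they did not differ by modality, this slope would not move. For a given δ, p = 0.5 is the worst case.

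**4. Step 3, compressed answers.** If phone answers have 0.7 of the spread, the telehealth slope is 0.7 × 0.30 = 0.21. With modality adjusted and no interaction, the pooled slope is (1 − p) × 0.30 + p × 0.21:
- p = 0.5: 0.255 (simulated 0.255)
- p = 0.2: 0.282
- p = 0.8: 0.228

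**The case against.** The strongest reply is that no aim targets the modality coefficient on patient outcomes. Aim 4 is about communication and discussion content, its conclusions are drawn only about those, and Step 3 already removes a constant shift. That stands, and it limits the damage. It does not answer Step 2, where modality is not among the listed controls, or the possibility of compressed answers. The modality coefficient will also be estimated for each of these outcomes, and readers will interpret it. The study is observational, so modality differences need care anyway. But no covariate can adjust for a difference in mode that coincides exactly with modality.

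A reader might also infer more than the documents support:

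- **All self-reported outcomes are affected.** They are not. Provider-rated alliance is self-completed in both settings.
- **The shift rivals the effect size of 0.2 in the power statement.** That figure is for provider implicit prejudice on communication styles, which coders rate from recordings. Survey mode cannot touch it, so it is no benchmark here.
- **The Black-White comparison is distorted.** The planned race contrasts (Aims 1 and 2) and race interactions (Aim 3) use recorded encounters. Patient race is not a named Aim 4 predictor and could enter only as a screened covariate.
- **Change from baseline is distorted.** At baseline, "Patients who meet the eligibility criteria will complete a 45-min baseline survey over the phone", so only in-person patients switch mode on the repeated scales. This would matter for a change score, but none is described.
- **Patients answer to the study staff who observed the visit.** The article does not say who makes the call. The team joins telehealth sessions with camera and microphone off, and in-person sessions are recorded too.

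**Conclusion.** The aliasing is exact and needs no assumption: for every patient-reported post-encounter outcome, survey mode is care modality under another name. The Aim 4 modality coefficient for these outcomes cannot be attributed to telehealth.

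The effect on the communication findings is conditional and probably modest. A constant shift leaves Step 3 slopes intact. It can move the Step 2 screen, by about 0.02 to 0.06 on a slope of 0.30 under the assumptions above, if communication also differs by modality. Step 3 slopes are affected only if mode changes spread or ceiling, which the documents neither show nor rule out. The size of any mode effect is assumed throughout. Aims 1 to 3 and chart-based testing completion are not affected.

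**What to change.** 1. Offer telehealth patients the existing electronic survey immediately after the session, and keep the phone call as a same-day backup. Both groups then share one main mode.
2. Record the mode used for each patient and run a sensitivity analysis, for example excluding phone completions. This should not be presented as fully separating mode from modality: in-person patients would still not be phoned, and those who need the backup call are self-selected.
3. Include care modality among the controls in the Aim 4 Step 2 partial correlations. This costs nothing.
4. If the phone-only procedure is kept, state that modality differences in patient-reported outcomes are not interpretable as telehealth effects.

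The cost is a change to one procedure, one recorded variable and one added control. The downside is that some telehealth patients will answer slightly later or need the backup call, so completion should be watched.

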#### Analysis of recorded genetic counseling encounters

We are going to use recorded genetic counseling encounters to assess both the observed quality of patient-provider communication and topic comprehensiveness of clinical discussion. This will be done by both observing recordings directly and analyzing verbatim transcripts of the recordings.

#### Patient-provider communication quality

The quality of patient-provider communication will be analyzed in two ways: global affect and linguistic patterns. To assess global affect, we will observe recordings and rate genetic counseling providers’ communication style by using the Global Affect Ratings from the Rotor Interaction Analysis System (RIAS) [47]. RIAS is the most commonly used method for coding genetic counseling encounters, [35, 36, 48] so use of RIAS enables us to directly compare our findings to those from prior research. We will use the Global Affect Ratings because the ratings reflect not only verbal behaviors (i.e., the context of speech) but also nonverbal (e.g., eye gaze, body posture, hand gestures) and paraverbal (e.g., tone, pitch, speed) behaviors, which tend to reflect an individual’s implicit prejudice [18–20]. The Global Affect Ratings consists of 14 categories: responsiveness/engagement; dominance/assertiveness; anger/irritability; anxiety/nervousness; hurried/rushed; friendliness/warmth; interest/attentiveness; depression/sadness; sympathy/empathy; emotional distress/upset; respectfulness; interactivity; scriptedness; and spontaneity. We will add a rating to assess the overall quality of patient-provider communication (e.g., smooth, awkward, good quality).

Each encounter will be rated by 15 racially diverse female coders. Coders will be all female because prior research has shown that women are more likely than men to make more accurate judgments of others’ characteristics [49]. Research has shown that over-thinking and over-reasoning can often disrupt the accuracy of global judgements and that people usually make better judgments when they do not try to explain their judgments [49–51]. Thus, we will not train coders to identify specific behaviors that might play role in making global judgments (e.g., smiling, frowning, eye contact). We will simply instruct them to report their impressions by using the full scale [24]. Coders will view encounters one by one and provide their ratings first for the 14 categories and then the additional items to assess overall patient-provider communication. The presentation order of the encounters will be randomized across coders. We will compute a composite score for each affective category and the overall patient-provider communication by averaging the ratings across coders. This composite score will be used in the statistical analysis.

To assess *the linguistic patterns of* patient-provider communication, we will both observe recordings and analyze transcripts. Specifically, we will examine genetic counseling providers’ linguistic patterns that reflect constructs associated with levels of implicit prejudice during racially discordant interactions in prior research, including social dominance, [52, 53] intergroup anxiety, [54–56] and avoidance (or lack of engagement) [57–59]. For social dominance, we will code: [1] patient-provider talk time ratio [25, 60]; [2] frequency of first person plural pronouns [26]; [3] turn-taking ratio [61, 62]; and [4] the number of interruptions and overlapping speech [63, 64]. For intergroup anxiety, we will code: [1] frequency of anxiety-related words (e.g., worried, afraid, nervous); [26] and [2] frequency of hesitation markers (e.g., uh, uhm, umm). For avoidance, we will code: [1] encounter length; and [2] frequency of back-channeling responses (e.g., Okay, yes, ah huh) [65].

Frequencies (i.e., first person plural pronouns, anxiety-related words, hesitation markers, back-channeling responses) will be assessed with the Linguistic Inquiry and Word Count (LIWC) software [66]. Each recording will be first transcribed verbatim, and then the verbatim transcripts will be further edited using the guidelines specifically developed for text analysis using LIWC [67]. Finally, the edited transcripts will be divided into two documents: patient vs. provider speech. The LIWC computes the percentage of use of words in more than 70 + word categories; it also enables researchers to create new word categories. For the current analyses, we will use both existing (i.e., pronouns, affective processes) and new (i.e., hesitation markers, back-channeling responses) categories.

The remaining coding will be conducted manually in steps. First, we will develop a linguistic codebook, which provides coding procedures, coding rules, descriptions, and examples of each linguistic pattern. Next, two senior research personnel will code a few transcripts and refine the linguistic codebook, and train two coders to apply the codes. The coders will then code all transcripts independently, while we check interrater reliability every 10 transcripts to prevent coder drift [68]. We will use the thresholds of *ICC* = 0.80 on 95% of codes [69]. We will use NVivo software to catalog and sort the coded data. Finally, we will take the findings from the analysis of linguistic patterns and create quantifiable units (Table 3) to be used in the statistical analysis.

**Table 3 Tab3:** An overview of the variables, measurements units, and regression types

Constructs and corresponding linguistic patterns		Units of measurement	Regression type

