**Fig. 1 Fig1:**
[figure not shown]
Our conceptual model of the role of genetic counselor’s bias in racial disparities in the genetic counseling processes

Research in healthcare disparities, social psychology, communication science, and our research all point to the role counselor bias may play in racial disparities in genetic counseling processes. Indeed, early studies of *simulated* genetic counseling encounters show that pro-White/anti-Black implicit prejudice leads to less individualized communication with patients [35] and may influence how genetic counselors help patients process emotional and cognitive information [36]. However, there are at least two major knowledge gaps that discourage us from starting with intervention research to address counselor bias. First, there has been no empirical documentation of the nature of such disparities in the *naturalistic* clinical setting. It is plausible that genetic counselors may communicate with patients differently in the naturalistic clinical setting than in a simulated one. More critically, the perspective and voice of actual patients are missing. Prior research shows standardized patient ratings of providers’ communication are different from actual patients’ ratings [37]. Notable, too, is that most research has not investigated trainees/students, yet trainees provide a significant proportion of genetic counseling. In the U.S., one-third of cancer genetic counselors report working at a university medical center, and one-third claim “student supervision” as one of their roles [11]. Thus, any generalizable research must include genetic counseling performed by supervised trainees.

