**(1) Social dominance**			
	Patient-provider talk time	Duration	Linear
	First person plural pronouns	Proportion	Linear
	Turn-taking	Frequency	Poisson
	Interruptions and overlapping speech	Frequency	Poisson

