Aim 1 (to compare/contrast the nature of patient-provider communication by patient race) examines Path A in our conceptual model. To test Path A, first, we will examine a numerical and graphical summary of descriptive statistics that will inform the distribution of the 15 outcomes (14 categorical variables and the overall patient-provider communication) and that may require data transformation. Then, we will conduct two separate analyses for communication and linguistic patterns. To examine how genetic counseling providers’ communication style differs by patient race, we will identify covariates by conducting bivariate correlations among all 15 outcomes and factors that were assessed in the baseline surveys (e.g., provider/patient demographics including sex, provider professional characteristics, patient perceived discrimination). Next, we will estimate a linear regression model for each outcome with the main effect of patient race, the main effect of care modality, a two-way interaction between patient race and care modality, and covariates identified as highly correlated with the outcomes. We will use GEE (which controls for the dependence in outcomes due to patients nested within providers) in these regressions, instead of multilevel modeling (which models the nonindependence in data), because there will not be enough upper-level units (i.e., counselors) to model random effects in our data. We will use the Bonferroni correction [93, 94] to address family-wise errors due to multiple comparisons. To examine which specific linguistic patterns differ by patient, we will conduct analyses in similar steps described above. First, we will identify highly correlated covariates by computing bivariate correlations among all quantified linguistic patterns and factors assessed in the baseline surveys. Next, we will conduct a regression for each quantified linguistic pattern with the main effect of patient race, the main effect of care modality, a two-way interaction between the two, and covariates using GEE and the Bonferroni correction. Type of regressions will depend on the measurement units.

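### Turn-taking is a ratio in the text and a raw Poisson count in Table 3, and as written neither is a usable measure of provider dominance

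*Protocol article*

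**What the plan says.** The protocol article's section on patient-provider communication quality sets out which linguistic patterns stand for which construct. The social-dominance list opens "For social dominance, we will code: [1] patient-provider talk time ratio [25, 60" and later includes "3] turn-taking ratio [61, 62]; and [4] the number of interruptions and overlapping speech [63, 64". The section does not say what is divided by what in the turn-taking ratio.

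Table 3, which the same section names as the source of the units for statistical analysis, places turn-taking under social dominance with the entry "Turn-taking Frequency Poisson". That is a count, not a ratio.

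Encounter length is an outcome in its own right under a different construct: "For avoidance, we will code: [1] encounter length".

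The Statistical analysis section (Aim 1) says of the linguistic models: "Type of regressions will depend on the measurement units". The stated terms are patient race, care modality, their interaction, and covariates screened from the baseline surveys. No exposure offset is mentioned. Encounter length is not a baseline-survey factor, so the screening would not bring it in. Coding detail is deferred: "First, we will develop a linguistic codebook, which provides coding procedures, coding rules, descriptions, and examples of each linguistic pattern".

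**The concern.** Two analysts working from this article could build different outcomes, one from the text and one from the table. Each version has its own difficulty as a marker of dominance.

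- **Ratio.** When two people talk, a turn normally ends because the other person starts. Both then have almost the same number of turns, whoever holds the floor longer.
- **Count.** A long encounter has more turns than a short one. Within encounters of equal length, a provider who speaks in long stretches produces fewer turns. The count therefore mixes length with exchange, and its relation to dominance is inverse. It shares the dominance set with interruptions, where more would ordinarily be read as more dominance.

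Aim 1 tests each linguistic pattern by patient race, and patterns identified there go on to Aim 3, where they are related to provider bias. A race difference in raw turn count could simply be a difference in encounter length. It could also be reported as dominance in the wrong direction, because the plan does not say which way to read it.

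**Working it through.** The plan gives no figure for this outcome, so there is nothing to reproduce. The check has three parts. Turn lengths, encounter lengths and third-speaker probabilities are all assumptions; the article gives none.

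**1. Ratio, exact bound.** If turns alternate between two speakers, their counts differ by at most one. With n turns for one speaker, the ratio lies between n/(n+1) and (n+1)/n.

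| n | lower | upper |
|---|---|---|
| 20 | 20/21 = 0.952 | 21/20 = 1.050 |
| 50 | 50/51 = 0.980 | 51/50 = 1.020 |
| 100 | 100/101 = 0.990 | 101/100 = 1.010 |
| 200 | 200/201 = 0.995 | 201/200 = 1.005 |

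**2. Ratio and count as the provider talks more.** For encounter length L, mean provider turn p and mean patient turn c (all in seconds), the expected total number of turns is about 2L/(p + c). With c = 8:

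- L = 1800, p = 10: 3600/18 = 200
- L = 1800, p = 60: 3600/68 = 52.9
- L = 3600, p = 10: 7200/18 = 400
- L = 3600, p = 60: 7200/68 = 105.9

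A simulation of 1,000 encounters per setting (exponential turn lengths, two speakers) agrees:

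| Provider mean turn | Talk-time ratio, 30 min | Mean turn ratio, 30 min | Turns, 30 min | Turns, 60 min |
|---|---|---|---|---|
| 10 s | 1.25 | 1.001 | 201 | 400 |
| 20 s | 2.52 | 1.004 | 129 | 258 |
| 40 s | 5.13 | 1.010 | 76 | 152 |
| 60 s | 7.61 | 1.016 | 54 | 107 |

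Across a sixfold change in provider turn length the mean turn ratio moves by about 0.015; its widest 95% range is 0.963 to 1.053. The count falls to about a quarter (54/201 = 0.27) and about doubles when the encounter doubles.

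Length can also reverse the ranking. A 60-minute encounter with 40-second provider turns (talk-time ratio 5.04) has 152 turns. A 30-minute encounter with 20-second provider turns (talk-time ratio 2.52) has 129. As an inverse marker, the raw count would call the longer encounter the less dominated one, although the provider's relative share of talk is twice as large. Turns per minute order the two as expected: 152/60 = 2.5 against 129/30 = 4.3. At a fixed turn length the rate hardly depends on duration: 201/30 = 6.7 and 400/60 = 6.7 at 10 s; 54/30 = 1.8 and 107/60 = 1.8 at 60 s.

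**3. A third speaker.** The background argues that "any generalizable research must include genetic counseling performed by supervised trainees", so a supervisor may sometimes speak. Let a third person take the floor after a patient or provider turn with probability 0.1 or 0.2, the provider following that person 80% of the time. The mean turn ratio then becomes 1.07 to 1.09 or 1.14 to 1.17. Across the same sixfold change in provider turn length it moves by only 0.01 to 0.03. The shift reflects the third speaker, not dominance.

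**The case against.** The strongest reply is that the article never defines the ratio. It cites two sources that are not available here and defers coding rules to a codebook, and Table 4 shows the team using turn concepts other than simple turn counts. The ratio could be something else, such as turns per minute. This stands. A reader might infer that the ratio equals 1 by construction; the document does not support that as a flat statement. It holds for provider over patient turns in a mainly two-party exchange, and only approximately.

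A reader might also take "Finally, the edited transcripts will be divided into two documents: patient vs. provider speech" as proof that turns are counted for two speakers only. That step prepares transcripts for the word-count software, whereas turn-taking is coded manually. Back-channel, overlap and third-speaker rules could all loosen strict alternation. This too stands, although the third-speaker check suggests a modest effect.

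Next, a reader might infer that the count points the wrong way and is uninterpretable. The article states no direction, and a coefficient of either sign can be read. At a fixed length the count tracks provider monologue strongly, but inversely, so it can serve as an inverse marker once length is handled. What is missing is the offset and the direction.

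Finally, Table 3 also labels talk time as a duration where the text says ratio, so its entries may be shorthand. That does not settle turn-taking: the row specifies Poisson regression, and following it literally means modelling a raw count with no length adjustment. The codebook argument does not remove this, because construct, unit and model are already stated in the article and do not agree.

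**Conclusion.** The point holds in limited form. The text and Table 3 specify different quantities under one label, and neither works as a dominance measure as written. The ratio, if it is provider over patient turns, carries almost no information on dominance. The count depends on encounter length, which the plan assigns to avoidance; it runs inversely to provider monologue at a given length and has no stated direction.

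The bound in part 1 rests only on alternation. The sizes in parts 2 and 3 rest on assumed turn lengths and illustrate direction and rough scale; they do not predict this study's data.

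Severity is minor. One of the eight patterns in Table 3 is affected, and neither the stated power calculation nor a main hypothesis depends on it.

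**What to change.** Make the linguistic-patterns text and Table 3 name the same quantity, and do not use a provider:patient ratio of turn counts. The preferred choice is turns per minute, fitted as a Poisson GEE on the turn count with log encounter duration as offset, so that the race coefficient is a log rate ratio. State in advance that fewer turns per minute is the unfavourable direction, and whether the measure is kept as an inverse dominance marker or moved to interactivity and engagement. The codebook should say how back-channels, overlaps and third speakers count towards turns.

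Dropping the item is possible but not needed. The Bonferroni gain is negligible: taking a 0.05 level and a family of eight, neither of which the article states, the threshold would move from 0.05/8 = 0.00625 to 0.05/7 = 0.00714.

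The cost is a few lines in the text, Table 3 and the codebook; encounter length is already being recorded, so no new data are needed. The downside is slightly less comparability with earlier work that used the turn-taking ratio label.
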